#### Data Capture

Immediately after initial login, participant information is captured as per the table in the Multimedia Appendix 1. Data capture then occurs on both the presearch and postsearch answer screens, as listed in Table 1. All system interactions will also be captured including (1) overall time spent searching for and answering each question; (2) dwell times before first query, on the SERP screen, on the document viewing screen, and on the answer screen; (3) the participant’s search query terms and resulting SERP; (4) documents selected from the SERP; (5) evidence selected by the participant from the documents they are viewing; and (6) relevance ratings by the participant of the documents they view (essential, helpful, duplicate-essential, duplicate-helpful, and not helpful). Multimedia Appendix 3 itemizes the search interaction times and how these relate to the study timings. Although desirable, it is not possible to question the participant regarding the utility of each search system because the user is not made aware of which search system is in use for each task.

Anonymity of the data collected is maintained by (1) identifying users and all of their interactions with a random user identification within the data capture system, (2) having no participant identification information stored in the same system database, and (3) capturing only generic participant information (see Multimedia Appendix 1) that could not be used to identify an individual.

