### Clinical Tasks

The criteria for task selection was that each task must (1) have answers able to be found in the literature, (2) be able to be answered with yes/no/conflicting information or a single-term/phrase response, (3) be credible to a practicing clinician, and (4) have nonobvious answers. Overall, 6 of the 16 clinical questions are those produced and used by Westbrook et al [16] and are reproduced here in Table 2. The tasks consist of real-life scenarios and a clinical question for each scenario. Westbrook et al derived the tasks using clinical experts and designed them to be clinically relevant and of mixed complexity. In addition, 4 questions are sourced from Hersh et al [18], which are also clinical questions and used for the same purposes as this study. Overall, 3 questions are modified from the text retrieval conference (TREC) 2015, clinical decision support (CDS) topic set [37]. These questions were provided with diagnoses, which our medical physician (DA, MBBS), modified into a question of a similar format to the other questions. Finally, our medical physician also devised a further 3 other clinical questions for the purposes of this test. Moreover, 2 general practitioners trialed all questions for suitability.

**Table 1 table1:** Data capture on the presearch and postsearch answer screens.

No	Data: purpose	Measurement	Presearch	Postsearch
1	Answer: Decision quality	Select (Yes/no/conflicting evidence/do not know) or type answer depending on the question	Yes	Yes
2	Confidence in answer: impact of the system on answer confidence	How confident are you in your answer? (1=no confidence, 2=a little confident, 3=moderately confident, 4=very confident, and 5=certain)	Yes	Yes
3	Perceived difficulty: relationship with time constraints and answer quality	How would you rate the difficulty of this clinical question? (presearch) and How would you rate the difficulty of the search for evidence for this task? (postsearch). (1=very easy, 2=easy, 3=neither easy nor difficult, 4=difficult, and 5=very difficult)	Yes	Yes
4	Perceived impact of time constraint on decision: relationship with decision quality and confidence	How would you rate the time you had available to make your decision? (1=not nearly enough time, 2=nearly enough time, 3=just enough time, 4=more than enough time, and 5=much more than enough time)	N/A	Yes

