### Statistical Analyses

To assess the impact of introducing the SML search system on clinical decision quality (RQ-1), each participant’s answer, both presearch and postsearch, will be coded to right (R) or wrong by comparing the participant’s answer with an expert judged assessment (gold answer) of each task. Samples for which (1) no evidence is captured and (2) no relevant documents are marked (either as essential or helpful), by the participant for their postsearch answer, will be discarded, as the value of the search system cannot be confirmed in these cases. Therefore, the decision quality is defined by the correct answer rate (number of right answers/total sample count (N)). A further detailed analysis will be performed of the collected evidence to identify tasks where the literature may contradict the gold answers. Where this occurs, the task answers will be reviewed by experts and overall correct rates adjusted.

To assess the significance of any change in the proportion of right or wrong answers, the McNemar test will be employed because it is a nonparametric test suited to a binary result, with samples taken at 2 points in time. Nonparametric is a better model to assume, given that the data distribution is unlikely to be regular because of the different medical groupings of participants. The sign test, which is also a nonparametric test, will be used to identify any significant changes to the correct rate. To assess any differences between the participant groups (nurses, doctors, and students), a Chi-square analysis will be performed. The participant’s confidence in their answers will be assessed presearch and postsearch to identify any significant changes relating to search intervention, also using chi-square analysis.

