To assess the impact of time constraints on clinical decision quality (RQ-2), the analyses above will be repeated with a breakdown by time constraint category, that is, 3, 6 and 9 min. In addition, an analysis of time-outs by constraint category will be conducted to assess the impact of time constraints on task completion. Time-outs are defined as samples where at the postsearch answer stage (1) the task timer reaches the constraint duration and (2) the participant provides no evidence to support their answer. It is assumed that in a time-out scenario, the participant was unable to complete the task. Significant differences by time-constraint category will be analyzed using the chi-square analysis. An analysis of variance (ANOVA) will be performed across confidence, difficulty, participant-perceived time impact assessments (impact of time on answer, evidence capture, and stress), and search behaviors, such as SERP dwell time, number of queries issued, number of documents opened, and the quantity of evidence items selected. To gain an understanding of the impact of providing a time constraint on the decision-making process, both the average time to search and the average proportion of available search time used will be evaluated and compared for the different task-timing samples. Tombros et al [67] used this proportional figure as a further gauge of participant stress and it can be compared with the reported stress by the participants.

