To assess the impact of search engine performance on clinical decision quality (RQ-3), a similar set of analyses will be performed as that for RQ-1, except broken down by search system (state-of-the-art and BM25). In addition, the same ANOVA methods employed for time-constraint categories in RQ-2 analysis will be performed. In addition, an ANOVA will be performed across system categories and system time constraints to identify cases where system performance effects may matter most. The impact of search engine performance on clinical decision time (RQ-3) will also be assessed by evaluating the postsearch task completion times for those tasks that were completed (ie, relevant documents and/or evidence identified). This is measured in 2 ways: (1) search time only and (2) search time plus time spent filling in the answer form. Differences in search times between the systems will be assessed using the chi-square analysis. Finally, a participant-derived performance assessment of the 2 systems can be constructed by building a graded query relevance (QREL) listing (standard format for representing relevance assessments in IR), by query, based on all participants’ relevance ratings. Using this QREL, a recomparison of the 2 systems can be evaluated and compared using the formal TREC evaluation results to provide better insight into any changes observed (or not) in the clinical decision and timing results for the 2 systems.

There are a number of potentially confounding factors within the experimentation. A covariant analysis (repeated measure ANOVA) will be performed on the task number, task at total duration point (for fatigue), and time transitions (eg, 3-min task to 6-min task and 3-min task to 9-min task).

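### The ANOVA of confidence by time limit and search system names no presearch-confidence covariate, although that rating is recorded for every task; the cost is some precision on a secondary outcome

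*Protocol article*

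**What the plan says.** Confidence is measured twice with one item. Under Data Capture: "Data capture then occurs on both the presearch and postsearch answer screens, as listed in Table 1". Table 1 lists "Confidence in answer: impact of the system on answer confidence", with the wording "How confident are you in your answer? (1=no confidence, 2=a little confident, 3=moderately confident, 4=very confident, and 5=certain", and marks it as collected both presearch and postsearch. All 16 stage 1 tasks are finished before stage 2 starts (Procedures).

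The Statistical Analyses section then uses confidence in two ways:

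- **Before against after (RQ-1).** "The participant’s confidence in their answers will be assessed presearch and postsearch to identify any significant changes relating to search intervention, also using chi-square analysis". For RQ-2, "the analyses above will be repeated with a breakdown by time constraint category, that is, 3, 6 and 9 min"; for RQ-3, "a similar set of analyses will be performed as that for RQ-1, except broken down by search system".
- **Between conditions (RQ-2 and RQ-3).** For time limits: "An analysis of variance (ANOVA) will be performed across confidence, difficulty, participant-perceived time impact assessments". For systems, "the same ANOVA methods employed for time-constraint categories in RQ-2 analysis will be performed", and a further ANOVA crosses system with time limit.

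The ANOVA text does not say whether the confidence outcome is the postsearch rating or the change from presearch, and it names no covariate. The closing paragraph on confounders plans a repeated-measures ANOVA with task number, point in the total duration and time transitions. Presearch ratings are not among them.

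**The concern.** Confidence ratings vary for reasons unrelated to the time limit or the search engine. People use the scale differently, some questions are easier than others, and a given person knows more about some questions than others. The presearch rating carries all three. It is also a true baseline: it is given before the participant meets any limit or system on any task.

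An ANOVA without that rating leaves in its error term whatever part of this variation the other model terms do not absorb. A real effect of time pressure or search engine on confidence is then harder to detect, most of all in the system-by-limit cells, which are the smallest. The before/after chi-square does not fill the gap. Repeating it within each limit or system shows whether confidence moved in that category; it does not estimate the difference between categories adjusted for where each participant started on each question.

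**Working it through.** **The plan's own figure.** The Sample Size section asks for 514 answers per time limit, from rates of 40% and 50%, 90% power and two-sided 5%. The unpooled two-proportion formula gives (1.960 + 1.2816)² × (0.40×0.60 + 0.50×0.50) / 0.10² = 10.507 × 0.49 / 0.01 = 514.9, so the figure reproduces. It concerns the correct answer rate. The article gives no sample size, effect size or correlation for confidence, so the correlations below are assumptions shown as ranges.

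**Answers available.** 96 × 16 = 1,536 answers; 1,536 / 3 = 512 per time limit; 1,536 / 6 = 256 per system-by-limit cell, all before discards.

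**Case A: answers treated as independent, no participant or task terms.** Adjusting for a baseline with correlation ρ multiplies the residual variance by 1 − ρ². For a contrast with 80% power unadjusted, the adjusted power is Φ[(1.960 + 0.8416)/√(1 − ρ²) − 1.960].

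| Assumed ρ | 1 − ρ² | Power |
|---|---|---|
| 0.1 | 0.99 | 80.4% |
| 0.3 | 0.91 | 83.6% |
| 0.5 | 0.75 | 89.9% |
| 0.7 | 0.51 | 97.5% |

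**If the ANOVA outcome were the change score.** With equal variances its variance factor is 2(1 − ρ), against 1 − ρ² for baseline adjustment. The ratio is (1 + ρ)/2, which never exceeds 1. At ρ = 0.5 the factors are 1.00 and 0.75. Adjustment is therefore at least as precise on either reading of the text.

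**Case B: participant and task terms already in the model.** These terms remove the differences between people and between questions, so only the remaining within-participant, within-task correlation ρr helps. The expected fall in standard error is 1 − √(1 − ρr²): 0%, 4.6% and 13.4% at ρr = 0, 0.3 and 0.5. A small simulation (96 participants, 16 tasks, limits rotated; assumed SDs of 0.6 for participant, 0.5 for task and 0.7 for residual; 15 runs per setting) gave these mean standard errors for one limit contrast:

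| Assumed ρr | Participant and task terms | Plus presearch rating | Fall |
|---|---|---|---|
| 0 | 0.0435 | 0.0435 | 0% |
| 0.3 | 0.0439 | 0.0417 | 5% |
| 0.5 | 0.0440 | 0.0380 | 14% |

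Formula and simulation agree. In the same simulation at ρr = 0, the model with time limit alone had a standard error of 0.0630, so participant and task terms by themselves cut it by 31% (1 − 0.0435/0.0630). In that setting most of the available precision comes from those terms, and the presearch rating adds the person-by-question part.

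**The case against.** The strongest reply is that the article is silent here rather than wrong. It does not fix the ANOVA outcome or list the model terms, and a covariate list for a secondary rating can sit in an analysis plan that is not shown. This stands in part, and it keeps the point small. But the article does publish a covariate list and does assign a role to presearch confidence, and neither brings that rating into the contrast between conditions.

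Three stronger readings are tempting, and the document supports none of them:

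- **A reader might infer that the presearch rating is collected and then wasted.** It is not. It enters the before/after chi-square, which is repeated by limit and by system.
- **A reader might infer that the comparison of limits or systems is biased.** The Task Order, System Rotation, and Task Timing section rotates both within participants and across tasks, so presearch confidence is balanced by design. Balance does not reduce residual variance, however, so the precision argument survives.
- **A reader might take the Case A figures as the expected gain.** They ignore the within-subject design that the article states. Under Case B the gain could be nil.

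Two further objections hold. Decision quality is defined by the correct answer rate, so confidence is secondary. And for difficulty the presearch item rates the clinical question while the postsearch item rates the search for evidence, so any gain from adjustment there is less certain.

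**Conclusion.** The point holds as an optional improvement in precision. The ANOVA of confidence by time limit, by system and by their combination names no presearch confidence term, although the identical rating exists for every participant and task and precedes any exposure to limit or system. The planned before/after chi-square does not supply the adjusted contrast. Validity is not in question.

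The size cannot be fixed from the document. Case A runs from almost nothing (80.4% at ρ = 0.1) to a large gain (97.5% at ρ = 0.7). Case B, which fits the stated within-subject design better, gives a standard error lower by roughly 0% to 14% for residual correlations from 0 to 0.5. Both cases rest on assumed correlations, and the Case B simulation also on assumed variances. Because participants search and read literature between the two ratings, a high correlation cannot be presumed.

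**What to change.** In the RQ-2 and RQ-3 paragraphs of Statistical Analyses:

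1. State that the confidence outcome is the postsearch rating.
2. Analyse it with a repeated-measures or mixed model on time limit, system and their interaction, with participant and task terms.
3. Add the same participant's presearch confidence on the same task as a covariate.
4. Optionally, treat the postsearch search-difficulty rating in the same way, with the presearch question-difficulty rating as covariate, and say that it is a related but different item.

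Ratings and behaviours without a presearch value (stress, time adequacy, search behaviours) can keep the model without a baseline term. The before/after chi-square can stay as the answer to its own question. The cost is a change of wording and one extra model term per adjusted rating; no new data are needed, and the article reports no results yet.

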The participant must complete the same 16 tasks in the same order as stage 1; however, the participant must now use Taskiir to help them answer the question and to find evidence to support their answer. Evidence is collected by the participant selecting text, images, or both from the source documents they read. The time allocated to search for each task is set according to the timing cohort the participant belongs to and will be one of 3, 6, or 9 min. The participant is told of the time allocation at the start of each question and a minute-by-minute countdown timer is always visible to the participant; warnings are given 30 seconds before time-out. At time-out, the screen is blocked, and the participant is taken to the task completion screen to enter their final details. Other methods of communicating the time limit were trialed during development of the system. In the end, the above method was chosen because it provided a balance between (1) making the participant aware of the time allocated for each question, (2) avoiding time anchoring (where the participant incorrectly assumed all questions are allocated the same time as the first question), (3) keeping them updated with the time remaining so they do not run out of time without warning, and (4) not distracting the participant with time information (eg, using a second-by-second countdown timer that diverted too much attention away from the task).

As this is the first such study measuring the impact of time variation, a few time limits covering a wide range are required to generate significant differences in the outcomes. A useful starting point to establish these time limits is the average completion time of 6.1 min per question, reported in the Westbrook study [33]. From the same study, the SD, based on the average completion times for each of the 8 questions, across 2 systems, is 3.1 min. Therefore, time limits are set at the average question answer time (6 min) and approximately 1 SD either side of this (3 and 9 min). These limits should induce time pressures for 84% of questions with a 3-min time limit, 50% of questions with a 6-min time limit, and 16% of questions with a 9-min time limit. From previous studies, realistic answer timeframes for busy clinicians should be below 5 min [3,15,35], so the 3 proposed time limit cohorts will encompass this pragmatic indicator of search time suitability.

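### The proportion of allowed search time used cannot be read as stress across the 3-, 6- and 9-min limits, because the limit is both its cap and its denominator

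*Protocol article*

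**What the plan says.** In the Statistical Analyses section, the RQ-2 paragraph plans two time summaries to show how a constraint affects the decision process: the average search time, and a second for which "the average proportion of available search time used will be evaluated and compared for the different task-timing samples". It adds that a cited study "used this proportional figure as a further gauge of participant stress and it can be compared with the reported stress by the participants". It gives no value that the proportion would be expected to take from the limit alone.

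The Procedures section (In Stage 2) shows that each task has a limit of 3, 6 or 9 min and that the limit is enforced: "At time-out, the screen is blocked, and the participant is taken to the task completion screen to enter their final details". The limits were chosen from "the average completion time of 6.1 min per question, reported in the Westbrook study" and an SD which, "based on the average completion times for each of the 8 questions, across 2 systems, is 3.1 min". From these the plan derives the shares it expects to be under time pressure: "84% of questions with a 3-min time limit, 50% of questions with a 6-min time limit, and 16% of questions with a 9-min time limit".

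Stress is also measured directly. Table 1, item 6, is a five-point postsearch rating of stress due to time pressure, and items 4 and 5 rate whether the time for the decision and for evidence collection was adequate.

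**The concern.** The samples being compared differ by design in one thing, the limit, and the limit is built into the measure twice. Search time cannot exceed it, and the result is divided by it. Someone who needs 5 min for a task uses 100% of a 3-min limit, 83% of a 6-min limit (5/6) and 56% of a 9-min limit (5/9), with no difference in pace or stress.

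A 3 > 6 > 9 min ordering is therefore expected in any case, and it is the ordering that would be reported as behavioural support for shorter limits raising stress. If self-reported stress shows the same ordering, the two would seem to corroborate each other, although each is expected to move with the assigned limit.

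The measure can also run against a real effect. The article's section on time constraints and time pressure notes that pressure can lead to a shallower search. Participants who coped in that way at 3 min and finished early would show a lower proportion.

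**Working it through.** **Inputs.** Limits L = 3, 6, 9 min; mean 6.1 min; SD 3.1 min; stated shares under pressure 84%, 50%, 16% (all from Procedures, In Stage 2). Assumptions: the mean and SD describe individual needed search times T, and the distribution of T is the same under every limit, so behaviour does not change.

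**Step 1: the plan's own figures.** With T normal, P(T > L) = 1 − Φ((L − mean)/SD).
- Mean 6.1, SD 3.1: 84.1%, 51.3%, 17.5%.
- Rounded mean 6, SD 3: 84.1%, 50.0%, 15.9%.

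The stated 84/50/16% is reproduced.

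**Step 2: the measure.** Time used is min(T, L), so the proportion is min(T, L)/L. This equals 1 when T ≥ L and T/L when T < L. For a fixed T it cannot rise as L rises, and from 3 to 9 min it strictly falls whenever T is below 9 min.

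**Step 3: size on the plan's figures.** For normal T with z = (L − 6.1)/3.1,

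E[min(T, L)] = L − [(L − 6.1)Φ(z) + 3.1φ(z)].

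- L = 3: z = −1.000; 3 − [−3.1 × 0.1587 + 3.1 × 0.2420] = 2.74 min; 2.74/3 = 91%.
- L = 6: z = −0.032; 6 − [−0.1 × 0.4871 + 3.1 × 0.3987] = 4.81 min; 4.81/6 = 80%.
- L = 9: z = 0.935; 9 − [2.9 × 0.8252 + 3.1 × 0.2576] = 5.81 min; 5.81/9 = 65%.

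The same expectation under other shapes, using 6.1 and 3.1 (for the truncated normal, before truncation):

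| Shape of T | 3 min | 6 min | 9 min | Fall, 3 to 9 min |
|---|---|---|---|---|
| Normal | 91% | 80% | 65% | 27 points |
| Normal, positive values only | 95% | 83% | 66% | 28 points |
| Gamma | 96% | 81% | 63% | 33 points |
| Lognormal | 98% | 82% | 63% | 35 points |

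**Step 4: sensitivity to the assumed mean and SD (gamma).**

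| Mean, SD (min) | Fall, 3 to 9 min |
|---|---|
| 6.1, 4.5 | 31 points |
| 6.1, 6.1 | 27 points |
| 5, 3.1 | 37 points |
| 8, 3.1 | 20 points |
| 4, 2 | 45 points |
| 3, 1.5 | 47 points |
| 13, 5 | 5 points |

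The size depends on how long searches would take without a limit. The direction does not.

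**Step 5: the companion summary.** Under the same unchanged behaviour, average time used is about 2.7 to 2.9 min, 4.8 to 5.0 min and 5.7 to 6.0 min at the three limits. It is capped too, so it also moves with the limit when nothing else does.

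**The case against.** The strongest reply is that little rests on this figure. RQ2 asks about decision quality, and the plan addresses it with correct-answer rates by limit and a time-out analysis. The proportion is a descriptive addition with no test or decision rule attached. Stress and perceived adequacy of time are rated directly and enter the planned ANOVA. Average minutes are reported alongside, so a careful reader would see minutes rise while the proportion falls. All of this stands, and it limits the consequence. It does not supply a no-effect benchmark, and it does not make the cross-limit reading valid.

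A second reply is that the text only reports how a cited study used the figure and says that it can be compared with reported stress. That is also right. A reader might infer that the plan will pool the limits, correlate the two quantities and claim that behaviour validates the ratings. The article states no such analysis, and any pooled correlation would have to be computed from invented stress scores.

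A third reply is that the plan treats a limit shorter than the time needed as inducing pressure, so using nearly all of a 3-min limit partly reflects the intended manipulation. As a description of how often the limit binds, that is fair. It is still not independent evidence of stress.

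Finally, the inputs are soft. The 3.1 min is an SD of question averages, not of individual searches. The 6.1 min comes from an earlier study with six evidence sources and a 10-min limit that was not enforced, and the present study stops its timer while the system searches. The size is therefore a model value.

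**Conclusion.** The point holds as a caution about interpretation. The raw proportion compared across the 3-, 6- and 9-min samples reflects the assigned limit, and neither its ordering nor its agreement across limits with reported stress is evidence about stress.

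The fall expected with no change in behaviour is about 27 to 35 points if 6.1 and 3.1 min describe individual search times, and about 5 to 45 points over other assumed means and SDs (47 in the most extreme run). The direction follows from the definition of the measure whenever some searches need less than 9 min; only the size rests on the assumptions.

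Two stronger readings are not supported. A reader might infer that RQ2 itself cannot be answered, but the correct-answer analyses, the time-out analysis and the sample size do not use this measure. A reader might also take a fall of about 30 points as a fact of this trial; it is a calculation from borrowed figures.

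**What to change.** 1. State that the raw proportion will not be interpreted as stress across limits. It may still be tabulated by limit as a description.
2. Relate the proportion to reported stress only within each limit, with limit as a stratum or factor and with participant and task effects.
3. If times are compared across limits, set the 3- and 6-min times against the 9-min times for the same tasks, capped at 3 and 6 min, and interpret only the departure from those values. Cut-off at 9 min does not disturb the benchmark, because a search stopped at 9 min has already passed both caps. Call it approximate: participants with 9 min are also told their limit and see a countdown, so their times may already be adapted and are not a true no-adaptation reference.

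The cost is analysis wording. Time per question is already captured (Data Capture section), and each task is performed under all three limits (Task Order, System Rotation, and Task Timing). The article describes the study as still under way, so the wording could be settled before the analysis.
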